### Participant timeline

The participant timeline is shown in Table 1. Briefly, all participants will undergo either PFM or sham-control therapy during 14 days screening period. They will be asked to follow up at 1 day, 14 days, 30 days, and 90 days after randomization.

**Table 1 Tab1:** The schedule of enrolment, interventions, and assessments

	Study period					
	Enrolment	Allocation	Post-allocation			Close-out
Timepoint	*− 14 days*	Day 0	*Day 1*	*Day 14*	*Day 30*	*Day 90*
Enrolment:						
Eligibility screen	X					
Informed consent	X					
Interventions:						
* PFM*		X				
* Sham-control*		X				
Assessments:						
Office BP measurement	X		X	X	X	X
24-h ambulatory BP measurement	X		X		X	X
History of diseases	X					
Physical examinations	X				X	X
Drugs use record	X			X	X	X
Antihypertensive drugs concentration tests	X				X	X
Blood routine	X		X		X	X
Biochemical test	X		X		X	X
C-reactive protein	X		X			
Biomarkers of acute renal injury	X		X			
ECG	X		X		X	X
Renal and renal artery ultrasound	X		X		X	X
Carotid ultrasound	X		X		X	X
Cardiac ultrasound	X					
MR imaging of perirenal fat	X				X	X
Functional MR imaging of hypothalamus	X				X	X

*PFM*, perirenal fat modification. *BP*, blood pressure, *ECG*, electrocardiogram *MR*, magnetic resonance

### Sample size

The PASS software (version 2011) was used to calculate the sample size. This study is a parallel group design, whose primary endpoint is the difference in office BP at 1 month compared with baseline. Our previous pilot study was a single-arm design recruiting 15 participants with mild-moderate hypertension for PFM therapy with results unpublished. Based on the outcome of the pilot study, the mean change in office SBP from baseline to 1 month was expected to 10 mmHg with a deviation of 13 mmHg in the PFM group. Meanwhile, we assumed that a mean difference of office SBP was 5 mmHg [15, 16] with a deviation of 13 mmHg in the sham control group. The sample size was calculated as 100 in each group with a power of 80%, a two-sided significance level of 5%, and a drop-out rate of 15%.

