### Statistical method

For the primary endpoint, a mixed-effect model for repeated measures (MMRM) adjusted with baseline office SBP will be used to compare the group difference of the office SBP changes from baseline to 1 month. For the secondary endpoint, we will also use the MMRM method adjusted with mean SBP or heart rate to assess the changes in the mean SBP or heart rate from baseline to each visit point. And LS-means method adjusted with baseline SBP or heart rate will be used to estimate the changes in SBP or heart rate and 95% confidence intervals. Imputation for missing values of the main indicator will be conducted using the Markov chain Monte Carlo (MCMC) model which will be performed as the result of the sensitive analysis. We predefine an adverse event of laboratory index that is significantly abnormal at follow-up compared with baseline. Detailed presentation of adverse events will be described and explore the relationship with PFM products. The efficacy analyses will be carried out based on the full analysis set and the pre-protocol set. All baseline characteristics analysis will be conducted on the basis of the full analysis set. The safety evaluation will be analyzed from the safety analysis set. A two-sided *P* < 0.05 will indicate significance in all statistical analyses used by the SAS software V.9.4 (SAS Institute, Cary, NC).

An interim analysis is planned when 50 subjects (100 subjects in total) are enrolled in each group and completed 1 month follow-up, which will be conducted by an independent data monitoring committee (IDMC). The purposes of the interim analysis are as follows: (1) to evaluate the safety (a necessary disruption of the study is considered when there are serious or expected adverse events) and (2) to assess the efficacy. This trial will be expected to terminate in advance if the hypothesis test *P* value is less than the boundary value of the interim analyzed *α* for the primary endpoint. And if the *P* value is greater than interim analyzed *α* with statistical power less than 60%, re-estimating the sample size is needed to make the final statistical power greater than 80%. In accordance with O’Brien-Fleming method, the interim analyzed *α* = 0.005, and final *α* = 0.048.

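### The stated inputs do not give 100 per group at 80% power: they need 126 to 128 per group, and 100 per group gives about 70%.

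*Protocol article*

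**What the plan says.** The Sample size section prints a complete set of inputs:

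- PFM group: the mean change in office SBP at 1 month "was expected to 10 mmHg with a deviation of 13 mmHg in the PFM group".
- Sham group: "a mean difference of office SBP was 5 mmHg [15, 16] with a deviation of 13 mmHg in the sham control group".
- Result: "The sample size was calculated as 100 in each group with a power of 80%, a two-sided significance level of 5" per cent.
- Attrition: "a drop-out rate of 15" per cent.

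The section mentions no covariate adjustment, no correlation with baseline and no one-sided test. Sequence generation confirms 1:1 allocation among 200 participants.

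The Statistical method section plans a baseline-adjusted MMRM for the primary endpoint and two-sided testing. It sets one interim analysis at 50 per group, with alpha 0.005 at the interim and 0.048 at the end. If the interim P value misses its boundary "with statistical power less than 60%, re-estimating the sample size is needed to make the final statistical power greater than 80" per cent.

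**The concern.** Every quantity needed for a two-sample comparison of means is given, so the result can be checked directly. At these inputs, 100 per group falls short of the required number of evaluable participants even before drop-out is allowed for. A slip in rounding or in the drop-out inflation therefore cannot explain it.

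At stake is the main design claim. If the true difference is 5 mmHg, the design at its fixed size misses it about 30% of the time and not 20%. A null result in this sham-controlled trial would then be read against a power the design did not have. The interim rule also uses power thresholds of 60% and 80%, so the monitoring committee should start from a correct design figure. The type I error rate is not affected.

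**Working it through.** **Inputs (all from Sample size unless noted).** Difference δ = 10 − 5 = 5 mmHg; SD σ = 13 mmHg in both groups; two-sided α = 0.05; power 80%; drop-out 15%; 1:1 allocation. Interim and final α of 0.005 and 0.048 come from Statistical method.

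**1. Attempt to reproduce 100 per group.**

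n = 2(z₀.₉₇₅ + z₀.₈₀)² σ²/δ² = 2(1.960 + 0.842)² × 169/25 = 106.1, so 107 evaluable per group. The exact noncentral-t calculation gives 108.

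- Dividing by 0.85: 107/0.85 = 125.9, so 126; 108/0.85 = 127.1, so 128.
- Multiplying by 1.15, a common shortcut: 124 to 125.
- At the final α of 0.048: 108 (normal) or 109 (t) evaluable, so 128 or 129 per group.

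None of these is near 100. The shortfall at α = 0.05 is 26 to 28 per group, or 52 to 56 in total.

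**2. Power of the stated size.** With 15% drop-out, 100 × 0.85 = 85 evaluable per group. The standard error is 13√(2/85) = 1.994, so δ/SE = 2.507. The normal approximation gives Φ(2.507 − 1.960) = 70.8%. By noncentral t:

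| Evaluable per group | Two-sided α | Power |
|---|---|---|
| 85 | 0.05 | 70.3% |
| 85 | 0.048 | 69.7% |
| 100 (no drop-out) | 0.05 | 77.2% |
| 100 (no drop-out) | 0.048 | 76.7% |

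With both looks (50 then 85 per group, α 0.005 then 0.048, bivariate normal), power is 70.4%.

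**3. What would give 100.** A one-sided 5% test needs 2(1.645 + 0.842)² × 169/25 = 83.6, so 84 (normal) or 85 (t). Then 85/0.85 = 100 exactly. With two-sided testing kept, 80% power at 85 evaluable per group needs one of the following (t-test):

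| Two-sided α | Detectable difference, SD 13 | SD needed, difference 5 |
|---|---|---|
| 0.05 | 5.62 mmHg | 11.57 mmHg |
| 0.048 | 5.65 mmHg | 11.50 mmHg |

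If the smaller SD is to come from baseline adjustment, the baseline–change correlation must be about √(1 − (11.50/13)²) = 0.47 at α = 0.048. That removes about 22% of the variance. At α = 0.05 the correlation is 0.46.

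**4. What the interim rule does at the design effect.** I simulated a true difference of 5 mmHg, SD 13 and 85 planned evaluable per group, with a look at 50 per group. The article does not define the power used at the interim, so two readings were tried.

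| Reading of interim power | No early stop, below 60% | No early stop, 60% to 80% |
|---|---|---|
| Conditional power, observed trend | 39% of trials | 11% |
| Power at the observed effect | 42% | 18% |

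Re-estimation would therefore be triggered in roughly two trials in five.

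**The case against.** Three arguments can be made for the plan.

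*The re-estimation rule protects power.* This stands in part. One might infer that the rule cannot help, because a design power of about 70% lies between the 60% trigger and the 80% target. That confuses design power with the interim figure, which varies from trial to trial and falls below 60% in about 39% to 42% of trials at the design effect. So the 30% miss rate belongs to the design at fixed size and not to the trial with re-estimation. How much power is recovered depends on a cap on the increase, which the article does not give. The rule still acts only after the interim and only when triggered, so it cannot make the sample-size statement correct.

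*The primary analysis is a baseline-adjusted MMRM.* Adjustment could raise power, and participants who leave before day 30 may still contribute day 1 and day 14 office readings. It would therefore be too strong to say that the trial's actual power is 70%. Without any covariate gain, 70% to 77% covers the range from 15% loss to none. But the calculation claims no gain and uses 13 mmHg as its SD. A gain that is neither stated nor justified does not validate it.

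*The trial is described as exploratory.* It nevertheless declares a primary endpoint, a power, a significance level and an efficacy stopping boundary, so the power figure should be right.

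A reader might also infer from 85/0.85 = 100 that the software was run one-sided. The match is exact and suggestive, but the software output is not shown. An SD of about 11.6 or a difference of about 5.6 mmHg would also lead to 100.

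**Conclusion.** The statement is wrong as written. On the article's own inputs, 80% power at two-sided 5% needs 107 to 108 evaluable participants per group, or 126 to 128 randomised. The stated 100 gives about 70% with the planned 15% drop-out, roughly 10 percentage points below the claim, and 77% with no drop-out at α = 0.05.

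These figures assume a two-sample comparison of changes with common SD 13 mmHg, a true difference of 5 mmHg, 85 evaluable per group, no covariate gain and no sample-size increase. The cause of the discrepancy is not documented. The figure 100 is consistent with a one-sided 5% t-test, and no more than that can be said. The conclusion does not depend on the cause, because the printed inputs and the printed result are incompatible.

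**What to change.** Keep the sample size at 200 and replace the power statement with, for example:

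> With 100 per group, 15% drop-out (85 evaluable), a difference of 5 mmHg, SD 13 mmHg and a final two-sided alpha of 0.048, power before any sample-size re-estimation or covariate gain is about 70%. The difference detectable with 80% power is about 5.65 mmHg (5.62 mmHg at alpha 0.05).

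If the sponsor wishes to keep 80% by taking credit for baseline adjustment, the section should state a residual SD of at most about 11.5 mmHg at alpha 0.048 (baseline–change correlation about 0.47) and justify it, for example from the pilot data. Raising the sample size would also reconcile the text, but the correction does not require it.

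The cost is a change of wording and a less favourable stated power. Recruitment, procedures and the alpha plan are untouched.

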### Recruitment

Potential eligible participants will be screened at the outpatient clinics of each study center. Advertisements of the trial introduction will be posted onsite at the hospital and on social media platforms.

### Assignment of interventions: allocation

#### Sequence generation

The randomized allocation sequence was generated at a 1:1 ratio in a completely random design among 200 participants by a statistician via the SAS 9.4 software (SAS Institute, Cary NC, USA) and integrated with a central computerized randomization system (Biomed Information Technology Co., Ltd. Beijing).

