### Trial design

This is an investigator-initiated, multicentered, randomized, sham-controlled, double-blinded, and exploratory clinical trial with a 3-month duration, which primarily aims to assess whether PFM therapy can reduce blood pressure in patients with grade one to two hypertension.

Eligible participants will be randomized at a ratio of 1:1 into an intervention group and a control group. The participants in the intervention group will receive PFM therapy with focused ultrasound, while a sham procedure will be performed for the participants assigned to the control group. All participants will be assessed for efficacy and safety at 24 h, 2 weeks, 1 month, and 3 months after PFM or sham procedure. The main indicators to evaluate efficacy are the changes in office BP and 24-h ambulatory BP. Adverse events will be recorded at each visit. Blood samples and urine samples will be collected, and imaging examinations will be performed at baseline, 24 h, 1 month, and 3 months. Participants are required to measure their office BP at a 2-week visit. Except for the operator who is responsible for focused ultrasound, all staff, including researchers, statisticians, and participants, are blinded to the groups of randomizations.

This protocol report follows the SPIRIT reporting guidelines [14].

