## Methods: participants, intervention, and outcomes

### Study setting

This trial is initiated by the Cardiology Department, The First Affiliated Hospital of Nanjing Medical University. Eligible participants with uncontrolled BP will be recruited at three implementation sites, including the First Affiliated Hospital of Nanjing Medical University (Jiangsu Province), Nanjing Jiangning Hospital (Jiangsu Province), and Suzhou Municipal Hospital (Jiangsu Province).

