#### Implementation

An independent randomization system account is created for investigators at each study site for the randomization implementation. Each investigator will log in to the system via a website to enter the randomization page, input the information of the participants, check the name and code of the study site, and confirm the randomization information. Then, the randomization code and allocated arm of the participant will be generated in the system background which is blinded for the investigators. Additionally, the operator at each study site will log in to the system using an independent account with the authority to view the allocated arms. At this time, the participants are successfully enrolled in this study.

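### Three sites share one unrestricted allocation list and the stated model has no site term: a small, avoidable loss of precision, and an interim trigger that does not match the allocation method

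*Protocol article*

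**What the plan says.** - **Sites.** Under Study setting: "Eligible participants with uncontrolled BP will be recruited at three implementation sites".
- **Allocation.** Under Trial design: "Eligible participants will be randomized at a ratio of 1:1 into an intervention group and a control group". Under Sequence generation: "The randomized allocation sequence was generated at a 1:1 ratio in a completely random design among 200 participants". Neither section mentions blocks or stratification.
- **Site is known at randomisation.** Under Implementation, the investigator must "check the name and code of the study site, and confirm the randomization information". Site is not said to influence the allocation.
- **Operators.** The same section says that "the operator at each study site will log in to the system using an independent account with the authority to view the allocated arms".
- **Primary model.** Under Statistical method, the MMRM is "adjusted with baseline office SBP will be used to compare the group difference" in office SBP change at 1 month. No other covariate is named.
- **Interim.** The same section says: "An interim analysis is planned when 50 subjects (100 subjects in total) are enrolled in each group", with 1-month follow-up complete. The significance levels are 0.005 at the interim and 0.048 at the end.

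**The concern.** Site could plausibly be related to the outcome. Each site has its own operator, who locates the target by ultrasound, and participants are screened in each centre's own outpatient clinic. A multicentre trial usually deals with this by balancing allocation within sites, by putting site in the model, or both. The article describes neither, although the randomisation system already records the site.

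Precision is at stake. If mean SBP change differs between sites, that variation stays in the error term, and a chance surplus of one arm at one site goes uncorrected.

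The interim wording raises a second, smaller issue. A list of this kind does not hold the arms level along the way, so 50 per group and 100 in total will usually not be reached at the same moment. A per-arm count of completers also needs access to the allocation, which the Blinding section withholds from investigators, statisticians and follow-up staff.

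**Working it through.** **Inputs from the article.** Difference 10 − 5 = 5 mmHg; SD 13 in each arm; two-sided 5%; power 80%; drop-out 15%; 100 per group (Sample size). Three sites (Study setting). Interim at 50 per group and 100 in total, with levels 0.005 and 0.048 (Statistical method).

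**Assumed, because the article gives no figures.** Participants per site, and the share R² of outcome variance explained by site among the enrolled participants.

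**1. The plan's own figures.** n per arm = 2(z₀.₉₇₅ + z₀.₈₀)² × SD²/difference² = 2(1.960 + 0.842)² × 169/25 ≈ 106.1, so 107 (108 with the t distribution). After drop-out: 107/0.85 = 125.9, so 126 (128 with t). The stated 100 is not reproduced. It matches a one-sided 5% test: 85/0.85 = 100. That is a separate point and is used here only for the starting power. With 100 × 0.85 = 85 evaluable per arm, the noncentrality is 5/(13√(2/85)) = 2.507 on 168 df, and two-sided power is 70.3%. The 0.005/0.048 pair gives an overall two-sided alpha of 0.0499 at half the information, so that figure holds.

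**2. Value of a site term.** Residual SD = 13√(1 − R²), with 85 per arm:

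| R² (assumed) | Residual SD | Power |
|---|---|---|
| 0 | 13.00 | 70.3% |
| 0.02 | 12.87 | 71.2% |
| 0.05 | 12.67 | 72.5% |
| 0.10 | 12.33 | 74.8% |

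A simulation (6,000 runs, 170 evaluable, total SD 13) compared the model without and with site. Power was 70.5% and 70.2% with no site variance, 69.6% and 71.6% with a 5% share, and 70.1% and 74.1% with a 10% share.

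**3. How uneven the sites could be.** Probability that at least one site splits 60:40 or worse:

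| Site sizes (assumed) | List is a permutation of 100 + 100 | Independent 1:1 assignment |
|---|---|---|
| 67/67/66 | 10% | 26% |
| 120/50/30 | 41% | 51% |
| 140/30/30 | 54% | 60% |

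**4. What such a split would do.** A 10% site share means a between-site SD of √(0.10 × 169) = 4.1 mmHg. Take a site of 67 at the edge of its 95% range under independent assignment (26 against 41), differing from the others by 4.1 mmHg. With 100 per arm, the estimate shifts by (0.41 − 0.26) × 4.1 ≈ 0.6 mmHg, against an assumed effect of 5.

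**5. The interim trigger.** Probability of exactly 50:50 at 100 randomised:
- independent assignment: C(100,50)/2¹⁰⁰ = 0.080, with a 95% range for one arm of 40–60;
- permutation of 100 + 100: C(100,50)²/C(200,100) = 0.112, with a 95% range of 43–57.

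Read as at least 50 in each arm, the trigger falls at a median of 106 or 104 randomised (95th percentile 121 or 113), before any drop-out.

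Relative efficiency of a split p is 4p(1 − p), so 40:60 keeps 4 × 0.4 × 0.6 = 96%. At 40:60 the information fraction is 0.48 and overall alpha is 0.0500, against 0.0499 at 50:50.

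**The case against.** **Unrestricted randomisation through a central system is valid.** This stands. A reader might infer that the treatment estimate is confounded with site or operator. The documents do not support that: chance imbalance is not bias, the standard error allows for it, and step 4 puts a fairly extreme case at about 0.6 mmHg. The endpoint is also a change from baseline with baseline adjustment, so a constant measurement offset at one site largely cancels. Only site differences in change matter.

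**The analysis plan may already include site.** This stands as a limit. The article names one covariate and does not say that site is excluded. If the plan has the term, that half of the fix is done.

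**Strong operator dependence is inferred.** Targeting is done by a person, but output power is calculated automatically, and the article reports no variation between operators or sites.

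**The trigger works on a sensible reading.** A reader might infer that the interim would rarely take place. That holds only if exactly 50:50 at exactly 100 is required. Read as at least 50 per arm, it comes a few participants later, with alpha and information almost unchanged. The central system or the IDMC could also supply a per-arm count.

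**A reader might conclude that allocation should move to site-stratified blocks.** That does not follow. The list for all 200 was already generated and built into the system, and 74 participants had been recruited by 8 February 2022. A change would mix two schemes, need ethics permission and make allocation within a site more predictable. It would not mend the trigger either: stratified blocks of 4 give exactly 50:50 at 100 only about half the time, and blocks of 6 about 42%.

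What remains is that the model as stated leaves site out when including it is almost free, and that the trigger wording does not fit the allocation.

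**Conclusion.** The point holds as a modest efficiency and wording matter. One unrestricted list over three sites, with baseline office SBP as the only stated covariate, leaves chance site imbalance uncorrected and any between-site variance in the residual. There is no bias in expectation and no inflation of type I error.

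The likely gain from a site term is about 2 to 4 points of power if site explains 5–10% of the variance, against a loss of about 0.3 points if it explains none. The variance share and the site sizes are assumptions. The starting power of about 70% comes from the separate sample-size discrepancy; it makes a cheap gain more welcome but is not evidence for this point.

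Defining the interim by total completers makes the trigger fit the allocation method. It does not correct an error in the inference.

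**What to change.** 1. Before unblinding, add site as a fixed effect to the primary MMRM and to the secondary MMRMs, and record this in the analysis plan if it is not already there. Cost: one line of model wording and 2 degrees of freedom.
2. Define the interim as the point at which 100 participants in total have Day 30 data, and drop the condition on each group. Cost: a wording change. The split at that point will vary (roughly 40–60 in one arm at the outside), with at most about 4% loss of efficiency and overall alpha still about 0.05. Nobody then needs the allocation to know when the interim is due.
3. Leave the existing randomisation list as it is.

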#### Concealment mechanism

The randomization codes were generated by a statistician and embedded in the computerized randomization system. The main investigators will not have permission to view the allocation except for the principal investigator of each study site and operators who are responsible for PFM operation. The principal investigators are only authorized for urgent unblinding when a serious complication related to the PFM procedure occurs.

